### 5.6. Use of Anti-Malarial Treatment for Malaria in Pregnancy

Subjects presenting with clinical symptoms of malaria (fever  $>37.5^{\circ}\text{C}$ , oral) and diagnosed (either by rapid diagnostic tests or microscopy) with malaria at any time during the study period will receive standard antimalarial treatment according to the local treatment guidelines for malaria in pregnancy, and will continue to participate in the study.

### **5.7. Treatment for Sexually Transmitted Infection**

Subjects diagnosed with *T. pallidum* at the baseline Day 0 of Visit 1 or any time during the study period will receive standard dosing regimen of benzathine penicillin G consistent with local ANC guidelines.

Subjects presenting with clinical symptoms of *N. gonorrhoeae*, *C. trachomatis*, *T. vaginalis* at any time during the study period will receive appropriate therapies according to local ANC guidelines for treatment of these diseases in pregnancy.

Please refer to Section 5.5 (Concomitant Medications) and/or drug inserts for further information regarding potential interactions between study drugs and other treatment agents.

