#### Key Secondary Efficacy Endpoints

1. Occurrence at birth of a LBW live neonates;
2. Occurrence of severe maternal anemia (Hb <8 g/dL) at 36-38 weeks of gestation;
3. Occurrence of anemia (Hb <11 g/dL) at 36-38 weeks of gestation;

4. Occurrence of placental parasitemia at delivery;
5. Occurrence of placental malaria as determined by histology;
6. Number of episodes of STIs per subject including *T. pallidum*, *N. gonorrhoeae*, *C. trachomatis*, during the study period following first dose (diagnosis based on clinical presentation any time from first IPTp dose to delivery and/or on laboratory test results between Weeks 36-38).

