#### Other Secondary Efficacy Endpoints

1. Hemoglobin concentrations at 36-38 weeks of gestation;
2. Occurrence at birth of a neonate with congenital abnormalities;
3. Occurrence of a perinatal or neonatal deaths;
4. Birth weight of the live-borne neonate (singleton);
5. Number of episodes of symptomatic malaria per subject anytime from first IPTp dose administration to delivery;
6. Occurrence of a subject requiring additional treatment for malaria during the study period following the first dose (diagnosed based on clinical presentation and/or lab test results);
7. Occurrence of peripheral parasitemia at 36-38 weeks of gestation;
8. Occurrence of peripheral parasitemia at delivery;
9. Occurrence of cord blood parasitemia at delivery;
10. Occurrence of STIs including *T. pallidum*, *N. gonorrhoeae*, *C. trachomatis* during the study period following first dose (diagnosed based on clinical presentation prior to Week 36-38 and/or lab test results between Week 36-38);
11. Occurrence of a positive result for *C. trachomatis* infection at 36-38 weeks of gestation (diagnosed based on lab result);
12. Occurrence of a positive result for *N. gonorrhoeae* infection at 36-38 weeks of gestation (diagnosed based on lab result);
13. Occurrence of a positive result for *T. pallidum* test at 36-38 weeks of gestation (diagnosed based on lab result);
14. Occurrence of a *T. vaginalis* infection at 36-38 weeks of gestation (diagnosed based on lab result);

15. Occurrence of bacterial vaginosis at 36-38 weeks of gestation (diagnosed based on lab result);
16. Occurrence of ophthalmia neonatorum (diagnosed based on lab test results) in the neonate;
17. Occurrence of bacterial infections including pneumonia and other lower respiratory tract infections anytime from first IPTp dose administration to delivery;
18. Occurrence of pre-eclampsia from Week 20 to delivery;
19. Occurrence of nasopharyngeal swabs positive for macrolide resistant and penicillin resistant *Streptococcus pneumoniae* at baseline, at Day 28 (window Day 28 - Day 42) post delivery, and at about 6 months following last IPTp course. This test will be done in about 600 subjects each from the AZCQ and SP arms from two or more sites.

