### **5.8. Treatment for Anemia in Pregnancy**

Subjects diagnosed with anemia at the baseline, Day 0 of Visit 1 or any other visits during the study period will receive the standard treatment according to local ANC guidelines.

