### **6.1.4. Visit 4: Follow-up Visit at Weeks 36 to 38 of Gestation**

The subject will have the following procedures performed at this visit at ANC:

- Concomitant treatment history;
- Vital signs;
- Routine Obstetric check up;
- Thick and thin peripheral blood smears (2 smears per subject);
- Hemoglobin level (with HemoCueTM);
- Urine analysis for glucose & proteins;
- A dried blood blot for measurement of *P. falciparum* genetic markers. The blot will be sent for resistance tests only if the smear is positive:
  - CQ resistance markers in AZCQ treatment group: Pfcrt/Pfmdr1;
  - SP resistance markers in AZCQ treatment group: pfdhfr/pfdhps.
- A blood sample for *T. pallidum* tests: Rapid Plasma Reagin (RPR) test with confirmatory Treponema Pallidum Particle Agglutination (TPPA) assay;
- An endocervical swab for *C. trachomatis* and *N. gonorrhoeae* Test (Amplicor CT/NG PCR);
- A vaginal swab for bacterial vaginosis (Gram stain);
- A vaginal swab for *T. vaginalis* (refer to lab manual for details);
- AE assessments.

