    - Treponema Pallidum Particil Agglutination Assay (TPPA): a confirmatory test when RPR is positive. This is a treponemal test for the serologic detection of antibodies to the various species including *T. pallidum*. The test is used to confirm the reactive results of a non-treponemal screening test for *T. pallidum* or as a diagnostic test in patients with a nonreactive nontreponemal test but with signs or symptoms suggestive of late syphilis.
- B. *N. gonorrhoeae* and *C. trachomatis* test at Weeks 36 - 38 of gestation: an endocervical swab will be collected and PCR assay (Amplicor CT/NG, Roche) will be used for analysis;

- C. Bacterial vaginosis at Weeks 36 - 38 of gestation: a vaginal swab will be collected for Gram staining;
- D. *Trichomonas vaginalis* at Weeks 36 - 38 of gestation: a vaginal swab will be collected for the lab test. Refer to lab manual for details.
- Clinical presentations/diagnosis at any time during the study period through Day 28 post delivery. This information will be recorded on related CRF pages.
  - Clinical episode of malaria: subjects presenting with clinical symptoms of malaria (fever  $>37.5^{\circ}\text{C}$ , oral) and diagnosed (either by rapid diagnostic tests or microscopy) with malaria;
  - Sexual Transmitted Disease (STIs): include *T. pallidum*, *N. gonorrhoeae*, *C. trachomatis*;
  - Bacterial infections including pneumonia and other lower respiratory tract infections.
- Subjects requiring additional treatments for malaria during the study period following the first dose (diagnosed based on clinical presentation and/or lab test results);
- *P.f.* genetic resistance marker tests at Weeks 36 - 38 of gestation: A dried blood blot will be collected from all subjects but tests will be done only from subjects with parasitemia. Polymerase Chain Reaction (PCR) assay will be used and following markers will be tested:
  - CQ resistance markers in AZCQ treatment group: Pfcrt/Pfmdr1;
  - SP resistance markers in SP treatment group: pfdhfr/ pfdhps.
- Macrolide and Penicillin resistance tests for *Strep. pneumoniae*:

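### Section 5.7 ties treatment of gonorrhoea, chlamydia and trichomonas to symptoms, so a symptom-free woman found positive by the trial's own Visit 4 test has no required treatment

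*Protocol*

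**What the plan says.** **Treatment rules.** Section 5.7 uses two different triggers. For syphilis the trigger is a diagnosis: "Subjects diagnosed with *T. pallidum* at the baseline Day 0 of Visit 1 or any time during the study period" receive benzathine penicillin. For the other three organisms it is symptoms: "Subjects presenting with clinical symptoms of *N. gonorrhoeae*, *C. trachomatis*, *T. vaginalis* at any time during the study period will receive appropriate therapies", with local ANC guidelines governing the choice of therapy. Section 5.8 again uses diagnosis: "Subjects diagnosed with anemia at the baseline, Day 0 of Visit 1 or any other visits during the study period" are treated.

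**Testing.** The Visit 4 list in Section 6.1.4 includes "An endocervical swab for *C. trachomatis* and *N. gonorrhoeae* Test (Amplicor CT/NG PCR" and a vaginal swab for *T. vaginalis*. Section 7.2 repeats the first of these for gonorrhoea and chlamydia: "test at Weeks 36 - 38 of gestation: an endocervical swab will be collected and PCR assay". Neither section, nor the Schedule of Activities and its footnotes, makes these swabs conditional on symptoms.

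**Endpoints.** Key secondary endpoint 6 counts episodes of syphilis, gonorrhoea and chlamydia, with "diagnosis based on clinical presentation any time from first IPTp dose to delivery and/or on laboratory test results between Weeks 36-38". Among the other secondary endpoints, item 11 is "Occurrence of a positive result for *C. trachomatis* infection at 36-38 weeks of gestation (diagnosed based on lab result", item 12 is the same for gonorrhoea, and item 14 is "Occurrence of a *T. vaginalis* infection at 36-38 weeks of gestation (diagnosed based on lab result".

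**Nearest other provision.** Section 6.1.8 (Unscheduled Visit) allows extra tests and treatments where local or national ANC guidelines recommend them. It creates no duty to act on a positive Visit 4 result.

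**The concern.** The protocol looks for infection in women without symptoms and counts what it finds, but its mandatory treatment sentence waits for symptoms. Followed exactly as written, it lets an infection that the trial itself has detected, weeks or days before delivery, go untreated unless the site or local practice steps in.

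The protocol's own background shows why this matters. Section 1.3.2.3 names untreated asymptomatic infection as a weakness of STI care and links STIs to preterm delivery, low birth weight, stillbirth and newborn illness and death. It also cites a Ugandan randomised trial of 4,033 pregnancies in which presumptive treatment, which does not wait for symptoms, improved maternal health and birth outcomes. What is at stake is the care of participants and their newborns. The validity of the efficacy comparison is not in question.

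**Working it through.** The protocol states no figure to reproduce. The check sets the provisions side by side.

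| Infection | Required-treatment trigger | Visit 4 test needs symptoms? | Laboratory positive counts as an endpoint? |
|---|---|---|---|
| *T. pallidum* | Diagnosis (5.7) | No | Yes: key secondary 6; other secondary 10 and 13 |
| *N. gonorrhoeae* | Symptoms (5.7) | No | Yes: key secondary 6; other secondary 10 and 12 |
| *C. trachomatis* | Symptoms (5.7) | No | Yes: key secondary 6; other secondary 10 and 11 |
| *T. vaginalis* | Symptoms (5.7) | No | Yes: other secondary 14 only |

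**Step 1, the gap.** In the last three rows a positive test without symptoms satisfies the endpoint but not the treatment trigger. In the syphilis row it satisfies both.

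**Step 2, does study drug close it?** Section 1.6.1.2 gives 3 × 1000 = 3000 mg azithromycin per AZCQ course and states that 2000 mg is needed for syphilis, chlamydia and gonorrhoea; 3000 exceeds 2000. Three courses are planned, the last no later than Week 36. Fewer gonorrhoea and chlamydia positives should therefore be expected in the AZCQ arm. An AZCQ woman who is still positive remains outside the rule, and no course is scheduled after Week 36. *T. vaginalis* is not in that dose statement. SP women receive no azithromycin from the trial and are barred from it by Section 5.5.

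**Step 3, time available.** The delivery week is assumed.
- Delivery at 40 weeks: (40 − 38) × 7 = 14 to (40 − 36) × 7 = 28 days after Visit 4.
- Delivery at 38 weeks: (38 − 38) × 7 = 0 to (38 − 36) × 7 = 14 days.
- Visit 6 is Day 28 to 42 after delivery, so it falls at least 0 + 28 = 28 days after the swab.

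A result may come too late for delivery, but a scheduled contact follows. The protocol gives no laboratory turnaround time.

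**Step 4, scale.** The prevalences in Section 1.3.2.3 are for symptomatic STIs, so they give no rate of symptom-free positives. A unit conversion is all that is possible. With 1:1 allocation, an arm has 2,602 / 2 = 1,301 to 5,044 / 2 = 2,522 women, so each 1% of an arm is 0.01 × 1,301 = 13 to 0.01 × 2,522 = 25 women, if enrolment is complete and all attend Visit 4. This is not an estimate of how many are affected.

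**The case against.** The best counter-case is that a treatment trigger and an endpoint definition serve different purposes and need not match. On that view the protocol is merely silent, and existing provisions lead a detected infection to care. Several parts of this have weight.

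- **Parallel rule.** Section 5.6 also requires symptoms, together with a diagnosis, before antimalarial treatment, although Visit 4 takes smears from all women. The symptom trigger is therefore not a slip confined to Section 5.7. That explains the drafting but supplies no duty to treat.
- **Syphilis is different.** Its screening is ordinary ANC practice (Section 7.2), which partly accounts for the wording. But Visit 4 tests for syphilis too, and that result does trigger treatment.
- **Other routes.** Section 6.1.8 permits guideline treatment. Section 8.4 makes a test result that needs intervention reportable as an adverse event. Section 12.2 binds the trial to GCP and the Declaration of Helsinki. These make treatment likelier, but none requires it. The lab manual is not available here; its scope as described in Section 7 is sample procedures and materials.
- **Neonatal cover.** Presumptive ophthalmia treatment at birth (Section 7.2) deals with one neonatal risk. It does not treat the mother.
- **AZCQ arm.** The azithromycin dose is a real mitigation for gonorrhoea and chlamydia, and it narrows the point to the SP arm for the most part.

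A reader might also infer more than the text supports. The protocol does not withhold or prohibit treatment; it leaves it optional. Nor does the gap bias the Visit 4 laboratory comparison, because the swab is taken before any treatment that its result could prompt.

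**Conclusion.** The point holds as a gap in participant care that the protocol's own wording creates. For three infections that the trial actively looks for, required treatment depends on symptoms, while detection and case counting do not. It goes beyond missing detail, because Section 5.7 states a trigger and that trigger leaves out women the trial knows to be infected.

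Its size is unknown and should not be given as a number of women; any percentage would be an assumption. For gonorrhoea and chlamydia the weight falls mainly on the SP arm, if azithromycin works as Section 1.6.1.2 expects. For *T. vaginalis* the protocol states no comparable treatment dose, so either arm may be concerned. No bias between arms is claimed, and the trial's conclusions are not threatened. This is a cheap improvement worth making, and no reason to doubt the design.

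**What to change.** 1. In Section 5.7, change the trigger for the three organisms to infection diagnosed clinically or by laboratory test, managed under local ANC guidelines.
2. Require positive Visit 4 results to be returned to the investigator promptly, before delivery where possible, and otherwise acted on by Visit 6.
3. In the SP arm, use a regimen without azithromycin where the guidelines offer one; Section 5.5 notes that Fansidar is compatible with antibiotics. Where they offer none, allow azithromycin for a confirmed infection and record it as an exception to Section 5.5. This provision is needed because Section 1.3.2.3 describes azithromycin as a recommended treatment for chlamydial and gonococcal infection, so guideline care and the Section 5.5 bar could conflict.

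**Cost.** Small reporting work and some added treatment. Treatment before delivery would probably be commoner in the SP arm. It could slightly reduce the contrast in ophthalmia neonatorum (other secondary endpoint 16, tested by PCR for gonorrhoea and chlamydia), in clinical STI episodes after Visit 4 (key secondary endpoint 6) and in birth outcomes. That is an acceptable price for treating a detected infection. The Visit 4 laboratory endpoints do not change, and laboratory staff can stay blinded as Section 5.2 provides.

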### **5.8. Treatment for Anemia in Pregnancy**

Subjects diagnosed with anemia at the baseline, Day 0 of Visit 1 or any other visits during the study period will receive the standard treatment according to local ANC guidelines.

## **6. STUDY PROCEDURES**

This study is exclusively conducted in pregnant women at ANC center or facility. Depending on when subjects enter the trial by gestational week, some subjects may have been to ANC prior to the first study visit. For such subjects, if results of required tests are available, then the test will not be repeated. The results will be transcribed to subject's Case Report Form as required following informed consent process is completed.

**Refer to Section 7 (Assessments) for details on the procedures performed in the study.**

### **6.1. Study Period**

#### **6.1.1. Visit 1: Baseline/Screening Visit/Treatment Course 1**

##### Day 0: Antenatal Care (ANC) Visit/Assessment of Study Eligibility

After informed consent is obtained, the subject must have the following procedures performed prior to the start of therapy:

- Medical history;
- Obstetrical history;
- Concomitant treatment history;
- Urine pregnancy test (if not done at any prior ANC visit for this pregnancy);
- Urine analysis for glucose and proteins;
- Complete physical examination;

- Vital signs;
- Routine obstetric checkup;
- Obstetrical ultrasound examination (if urine pregnancy test is positive);
- Hemoglobin level (with HemoCue™);
- *T. pallidum* screen test if not done at previous ANC check up;
- Nasopharyngeal swab test for macrolide resistant and penicillin resistant *Streptococcus pneumoniae* in approximately 600 subjects each in AZCQ and SP arms from 2 or more sites as feasible.

#### Day 0: Post Assessment of Eligibility/Treatment Course 1

Subjects who have met all inclusion/exclusion requirements and are eligible to be randomized will have the following procedures performed:

- Randomize to one of the study treatments;
- Administer treatment (AZCQ or SP);
- Assess adverse (AE) events;
- Provide LLINs.

#### Days 1 and 2: Home Visit (by the fieldworker)

- For subjects in the AZCQ group: the second and third dose of AZCQ will be administered to subject on Day 1 and Day 2 at home under supervision of the fieldworker. The installation of LLINs will be verified during the Day 1 visit; AE assessment at both home visits;
- For subjects in the SP group: home visit will be conducted on Day 2 to confirm the installation of LLINs and assess AEs.

#### **6.1.2. Visit 2: Treatment Course 2**

The time interval between the visits for treatment course 1 and the treatment course 2 will be 4-8 weeks. The subject will have the following procedures performed:

#### Day 0: ANC Visit:

- Concomitant treatment history;
- Vital signs;

- Routine obstetric checkup;
- Hemoglobin level (with HemoCue™);
- Urine analysis for glucose and proteins;
- Drug administration (AZCQ or SP);
- AE assessments.

#### Days 1 and 2: Home Visit

- For subjects in the AZCQ group: the second and third dose of AZCQ will be administered to subject on Day 1 and Day 2 at home under supervision of the fieldworker. AE assessment at both home visits;
- For subjects in the SP group: home visit will be conducted on day 2 to assess AEs.

#### **6.1.3. Visit 3: Treatment Course 3**

The time interval between the visits for treatment course 2 and the treatment course 3 will be 4-8 weeks. The third treatment course should be given to subjects prior to or during 36 weeks of gestation. The subject will have the following procedures performed:

#### Day 0: ANC Visit

The subject will have the following procedures performed at ANC:

- Concomitant treatment history;
- Vital signs;
- Routine obstetric checkup;
- Hemoglobin level (with HemoCue™);
- Urine analysis for glucose and proteins;
- Drug administration (AZCQ or SP);
- AE assessments.

### Days 1 and 2: Home Visit

- For subjects in the AZCQ group: the second and third dose of AZCQ will be administered to subject on Day 1 and Day 2 at home by the fieldworker(s). AE assessment at both home visits;
- For subjects in the SP group: home visit will be conducted on day 2 to assess AEs.

### **6.1.4. Visit 4: Follow-up Visit at Weeks 36 to 38 of Gestation**

The subject will have the following procedures performed at this visit at ANC:

- Concomitant treatment history;
- Vital signs;
- Routine Obstetric check up;
- Thick and thin peripheral blood smears (2 smears per subject);
- Hemoglobin level (with HemoCueTM);
- Urine analysis for glucose & proteins;
- A dried blood blot for measurement of *P. falciparum* genetic markers. The blot will be sent for resistance tests only if the smear is positive:
  - CQ resistance markers in AZCQ treatment group: Pfcrt/Pfmdr1;
  - SP resistance markers in AZCQ treatment group: pfdhfr/pfdhps.
- A blood sample for *T. pallidum* tests: Rapid Plasma Reagin (RPR) test with confirmatory Treponema Pallidum Particle Agglutination (TPPA) assay;
- An endocervical swab for *C. trachomatis* and *N. gonorrhoeae* Test (Amplicor CT/NG PCR);
- A vaginal swab for bacterial vaginosis (Gram stain);
- A vaginal swab for *T. vaginalis* (refer to lab manual for details);
- AE assessments.

### **6.1.5. Visit 5: Follow-up Visit at Delivery**

#### **6.1.5.1. Follow Up Visit at Birth in Case of Hospital Delivery (At Birth)**

Every attempt should be made to have the subject deliver in hospital setting and data will be collected at birth. The following procedures will be performed at the time of delivery in hospital:

##### For mothers:

- Pregnancy outcomes;
- Limited physical examination;
- Vital signs;
- Hemoglobin level (with HemoCue™);
- Peripheral blood smears from the mother (2 smears per subject);
- Placental blood smears (2 smears per subject);
- Cord blood smears (2 smears per subject);
- A sample of the placenta tissue for histological examination as feasible (size: about 2cm x 2cm x 1cm);
- Concomitant treatment history;
- AE assessments.

##### For neonates:

- Birth weight of the neonate;
- General physical exam of the neonate;
- Lab diagnosis of ophthalmia neonatorum: collection of conjunctival exudates from neonates with purulent discharge for the lab test before the presumptive treatment is given. The standard empiric regimen of ophthalmia neonatorum presumptive treatment will be given to all neonates at birth per local treatment guidelines;
- AE assessments;
- Outcome research/resource utilization question.

#### **6.1.5.2. Follow Up Visit at Birth in Case of Home Delivery (Within 2 Days of Subject Reporting Delivery)**

Subjects will be encouraged to deliver in hospital. In case that the subject gives birth at home (home delivery), the subject will be asked to contact the study sites and report delivery within 24 hours of delivery. Fieldworker should visit the subject at home thereafter within 2 days of subject reporting delivery, and collect and/or transcribe data required in the study.

The following data will be collected and/or transcribed by fieldworker(s) if available.

##### For mothers:

- Pregnancy outcomes;
- Vital signs;
- Concomitant treatment history;
- AE assessments.

##### For neonates:

- Birth weight of the neonate;
- General physical exam of the neonate: the data will be collected or transcribed if available;
- AE assessments;
- Outcome research/resource utilization question.

